### Assignment of intervention

Each bottle of IMP, whether the active medication or placebo, has a unique identification number. Each participant is assigned a unique identification number, which will be used throughout the duration of their treatment. When a participant’s identification number is entered into the randomization system, the algorithm will randomly allocate them to a study arm and notify the unblinded members of staff. At each monthly visit, pharmacy staff will assign a specific bottle of IMP to the participant. Only pharmacy staff dispensing the IMP and the pharmacy monitor (a clinical research associate) will be unblinded. The blinded members of staff include all research team members at site level including the chief investigator, each study site’s principal investigator, researchers undertaking assessments at each time point and trial statisticians. Participants will remain in their allocated treatment arm for the duration of the study, even if they discontinue taking their IMP.

### Emergency unblinding

Emergency unblinding and medical information will be provided by ESMS Global Ltd (London, UK). Each randomised subject will be given a card with telephone numbers to use for unblinding and emergency contact details. Subjects will be requested to carry this card with them at all times whilst participating in the trial. Only healthcare professionals who have direct responsibility for the care of trial participants, clinical trial investigators, pharmacists and the staff of King’s Health Partners Clinical Trials Office are authorised to request unblinding.

### Data collection and management

The trial data will be held in a customised electronic database (Infermed MACRO, Elsevier Ltd, version 4, London, UK), created and maintained by King’s Clinical Trials Unit. All source data will be collected directly on paper worksheets and then entered into an online case report form. The data entry screens will resemble the paper forms as closely as possible to minimise transcription errors. MACRO allows for data entry checks thereby enhancing data accuracy. Data can be extracted from the database for checks and analysis. All personal information collected on DFEND trial participants and on potential participants will be treated as confidential and will be handled according to good clinical practice guidelines, associated standard operating procedures, the Data Protection Act 1998 and the European General Data Protection Regulations [48]. All electronic files containing personal information will be held only on password-protected computers. The computers themselves will be kept securely. All other trial information, such as the trial master file, source notes and data code definitions, will be stored in a lockable fireproof facility that can be accessed only by delegated DFEND trial staff.

### Statistical analysis

Full details of the statistical analyses will be specified in a statistical analysis plan written in collaboration with the trial statisticians.

Descriptive analyses, recruitment rate, consent rate, loss to follow-up, departures from randomised treatment and the prevalence of serious adverse events post-randomisation will be reported and summarised by treatment arm over the course of the study. All causes of withdrawal from the randomised treatment will be reported.

Analyses will be carried out by the trial statistician, who will remain blinded until all analyses are completed. The analysis of vitamin D concentrations in blood samples taken at 6 months, which is a secondary outcome, will be carried out after all other analyses are completed, as there is a high expectation that the mean concentration will be higher in the intervention group.

An intention-to-treat analysis of the effect of vitamin D supplementation on the primary PANSS outcome will be conducted using linear mixed modelling. All the available follow-up data from the randomised participants will be modelled. The analysis model will include treatment arm (vitamin D or placebo), time (3 or 6 months), baseline PANSS and randomisation stratifier (ethnicity) as explanatory variables. The model will also contain a subject-varying random intercept to account for any correlation between the repeated measures. Treatment effects on the other secondary outcomes at 6 months will be assessed using similar modelling techniques, employing generalisations to non-normal data where necessary.

To address the secondary research objectives, we will also estimate treatment effects for the subpopulation who were vitamin D insufficient at baseline in terms of primary and secondary outcomes, except for 25OHD blood concentrations, by including relevant interaction terms between baseline vitamin D insufficiency status and treatment group in the statistical models.

We expect that some data will be missing in the post-treatment outcome variables. The linear mixed modelling analyses are based on maximum likelihood and will provide valid inferences under a missing-at-random missingness mechanism. We will explore predictors of missingness. If deemed suitable for adjustment, we will include these as explanatory variables in the analyses. If post-randomisation variables are identified, a multiple imputation model will be considered instead [49].

No interim analysis will be carried out. There are no formal prespecified stopping rules.

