**Methods/design:**

The DFEND study is a multicentre double-blind placebo-controlled parallel-group trial of vitamin D supplementation in people with early psychosis. Patients with an ICD-10 diagnosis of functional psychosis will be randomised in a 1:1 ratio to receive either 120,000 IU/month of vitamin D (cholecalciferol) or a matched placebo for 6 months. The primary outcome is the total Positive and Negative Syndrome Scale (PANSS) score at the 6-month follow-up for all patients. Secondary outcomes include assessment of mood (Calgary Depression Scale), general function (Global Assessment of Functioning), cardiovascular risk (body mass index, waist circumference, C-reactive protein, cholesterol and HbA1c) and vitamin D levels at the 6-month follow-up. Additionally, 3- and 6-month total PANSS scores will be analysed for those with inadequate vitamin D levels at the baseline.

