## Method/design

### Aims and objectives

The primary objective of the trial is to determine whether adding a monthly supplementation of 120,000 IU of vitamin D_3_ (cholecalciferol) to the standard treatment is more efficacious than a placebo in improving outcomes (PANSS) at the 6-month follow-up after an FEP. Secondary objectives are to examine the total PANSS score at 3 months, PANSS sub-scores at 3 and 6 months, along with a broader range of clinically relevant outcomes including Global Assessment of Function (GAF), the Calgary Depression Scale (CDS), cardiovascular risk markers and 25OHD concentrations. Here we report the DFEND study protocol according to SPIRIT guidelines (see Supplementary Material Additional file 1 for the SPIRIT Checklist).

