#### Primary outcome

The primary outcome is symptom severity, as assessed via total PANSS scores at 6 months after randomisation [38]. PANSS assesses symptom severity across three domains: positive symptoms (seven items), negative symptoms (seven items) and general psychopathology (16 items) [38]. A total PANSS score is derived by summing scores across the three domains. Scores range from 30 to 210, with higher scores depicting greater symptom severity. In terms of reliability, α = 0.73, 0.83 and 0.79 for the positive, negative and general psychopathology scales, respectively [38]. All researchers will undergo two thorough stages of in-house PANSS training. Firstly, trainee researchers will watch and rate two PANSS training videos on two separate occasions, followed by feedback and discussion with the trial manager. Secondly, trainee researchers will shadow an experienced member of the team and observe real-world PANSS interviews, after which they will rate the interview to become familiar with the rating scale. Researchers will then be permitted to conduct the PANSS assessments independently. Researchers will also be required to attend a training session every six months to maintain their reliability throughout the trial.

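### The primary mixed model, as published, has no treatment-by-time term, so its arm coefficient averages the 3- and 6-month effects, while the declared primary outcome is at 6 months

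*Protocol article*

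**What the plan says.** The target is fixed at one time point. Under Primary outcome: "The primary outcome is symptom severity, as assessed via total PANSS scores at 6 months after randomisation". Under Aims and objectives, the question is whether vitamin D "is more efficacious than a placebo in improving outcomes (PANSS) at the 6-month follow-up after an FEP". The Sample size section also places the primary outcome at the 6-month follow-up.

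Month 3 is kept separate and secondary: "Secondary objectives are to examine the total PANSS score at 3 months, PANSS sub-scores at 3 and 6 months". The abstract adds that "3- and 6-month total PANSS scores will be analysed for those with inadequate vitamin D levels at the baseline".

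The Statistical analysis section then describes one model for the primary outcome. On the data: "All the available follow-up data from the randomised participants will be modelled". On the fixed effects: "The analysis model will include treatment arm (vitamin D or placebo), time (3 or 6 months), baseline PANSS and randomisation stratifier (ethnicity". On the covariance: "The model will also contain a subject-varying random intercept to account for any correlation between the repeated measures". The subgroup question is handled by "including relevant interaction terms between baseline vitamin D insufficiency status and treatment group in the statistical models". That is the only interaction the section names. Full details are deferred to a statistical analysis plan.

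**The concern.** Month 3 and month 6 scores both enter as outcomes. With arm and time as main effects only, the model assumes the same arm difference at both visits and returns one number for it. The protocol asks for two numbers, one primary and one secondary.

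The consequence runs in both directions. If the effect is larger at 6 months than at 3, the reported primary estimate is too small and power may be lost. If there is an effect at 3 months that has gone by 6 months, the model can report a benefit that does not exist at the declared time point. The fitted model also has no separate 3-month effect to report. A subgroup model that adds only insufficiency-by-treatment gives one averaged effect in each vitamin D stratum, although the abstract promises 3- and 6-month scores for that subgroup.

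**Working it through.** **1. The plan's own figure.** The Sample size section gives SD 15.0, alpha 0.05 (taken as two-sided) and 80% power with 200 to 180 participants, and states detectable differences of 6 to 6.3. The formula is δ = SD × √(4/N) × (1.96 + 0.84).
- N = 200: 5.94 (5.97 with the t distribution).
- N = 180: 6.26 (6.30 with the t distribution).

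The figures reproduce, and they are for a comparison at a single visit. The sample size arithmetic is not at issue.

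**2. Inputs for the model.**
- From the article: SD 15; 240 randomised with 20% attrition, so 96 per arm at 6 months.
- Assumed, because the article gives none of them: correlation of baseline with follow-up r = 0.5 (range 0.4–0.6); residual correlation between the visits ρ = 0.5 (range 0.4–0.7); n₂ = 96 per arm with both visits and n₁ = 12 per arm with month 3 only; the true effects at each visit.
- Residual variance: σ² = 225 × (1 − 0.5²) = 168.75.

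**3. What the arm coefficient estimates.** Under a random intercept, generalised least squares gives

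w₃ = [n₂/(1+ρ) + n₁] / [2n₂/(1+ρ) + n₁] = (64 + 12)/(128 + 12) = 0.543.

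The coefficient is therefore 0.543 × (3-month effect) + 0.457 × (6-month effect). With complete data n₁ = 0 and the weight is exactly 0.50. Over the assumed range it stays between 0.50 and 0.55.

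**4. Standard errors.**
- Model as listed: √[2σ² / (2n₂/(1+ρ) + n₁)] = √(337.5/140) = 1.55.
- 6-month contrast with treatment-by-time: the per-arm information matrix, times σ², is [[140, −64], [−64, 128]], with determinant 13,824. The SE is √(337.5 × 140/13,824) = 1.85.

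**5. Results.** Power is from the normal approximation, two-sided 0.05. Central values use r = ρ = 0.5, and ranges cover the grid in step 2.

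| True effect at 3 / 6 months | Estimate, model as listed | Rejection, model as listed | Rejection, 6-month contrast |
|---|---|---|---|
| 0 / 6 | 2.7 | 42% (34–51%) | 90% (86–95%) |
| 3 / 6 | 4.4 | 80% | 90% |
| 4.5 / 6 | 5.2 | 92% | 90% |
| 6 / 6 | 6.0 | 97% | 90% |
| 6 / 0 | 3.3 | 56% (47–65%) | 5% |

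For example, for 0 / 6: 0.457 × 6 = 2.74; 2.74/1.55 = 1.77; power = Φ(1.77 − 1.96) ≈ 42%.

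**6. Independent check.** Mixed models were fitted to simulated data with within-person correlation 0.5, no baseline correlation and 100 replicates per scenario. With effects 0 / 6, the listed model gave 2.8 and rejected in 33% of replicates, against 5.8 and 77% for the 6-month contrast. With effects 6 / 0, it gave 3.2 and 39%, against 0.1 and 5%. With a constant effect of 6, both gave 5.8. Direction and size agree.

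**The case against.** The strongest reply is that this is a condensed article. It defers full details to an SAP that is not shown, it says the model will include certain variables without saying main effects only, and the 6-month target is unmistakable elsewhere. A competent statistician may well fit the interaction and report the 6-month contrast. A reader might infer from the listed terms that the trial will certainly estimate the wrong quantity. The documents do not support that, because the SAP may already contain the missing term.

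The point survives because the article does more than stay silent. It lists the fixed effects and the random effect, and in the next paragraph it names an interaction where one is wanted. Followed as written, that specification does not match the declared outcome.

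Two other stronger readings also go too far. One is that the trial cannot produce 3-month effects. Nothing bars a separate 3-month model, and the subgroup text speaks of relevant interaction terms in the plural; what holds is that the model described gives no separate 3-month effect. The other is that the effect must build up, so that dilution is certain. The article gives a fixed monthly schedule but no time course of response, so the 3-month effects above are only illustrations.

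It is also fair that the pooled model can gain power. With effects of 4.5 and 6 it has about 92%, against 90% for the 6-month contrast, although its estimate of 5.2 still understates the 6-month effect.

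**Conclusion.** The point stands for the model as published. Its arm coefficient is a roughly equal average of the 3- and 6-month effects and equals the declared primary effect only if the effect is constant over time, an assumption the article neither states nor justifies. That mismatch follows from the listed terms and does not depend on the assumed inputs.

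The size of the error does depend on them. It is nil for a constant effect and modest for a mild build-up. It is large when the effect is present at one visit only: the estimate is then about half the true effect at that visit, or a benefit at 6 months is declared in about half of trials where there is none. Because the primary result is affected, this should be corrected or clarified before the unblinded results are read.

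**What to change.** In the Statistical analysis section, add treatment-by-time to the primary model. State that the primary result is the model-based treatment contrast at 6 months and that the 3-month contrast from the same model is secondary. Make the subgroup model time-specific too, for example with a treatment-by-time-by-vitamin D status term together with its lower-order terms. Check the SAP and make the two documents agree; if the SAP already has these terms, only the article's description needs correcting. A baseline-by-time term and an unstructured covariance are optional, since neither is needed to identify the 6-month contrast.

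The change takes a sentence or two and no new data. Its price is precision if the effect really is constant: at assumed correlations of 0.5 the SE rises from about 1.55 to 1.85, and power for 6 points falls from about 97% to 90%, still above the 80% used in the Sample size section.

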### Sample size

Based on the number of new cases presenting to FEP services and annual counts of FEP patients recruited into similar studies, we predicted a recruitment and randomization rate of 120 patients per year for a total of 240. For the primary outcome (measured at the 6-month follow-up), we assumed a 20% attrition rate. Thus, the effective sample size is 192 (96 in each trial arm).

In the PUMP Study [46] (*n* = 190), the mean total PANSS score (and standard deviation) for patients with FEP was 58.1 (15.0). For the power analyses, we modelled two plausible scenarios using 80% and 90% power, respectively, with alpha = 0.05 for both scenarios. Based on alpha = 0.05, power = 80%, and samples with between 200 and 180 participants, we will confidently be able to detect group differences in mean total PANSS score of between 6 and 6.3. This equates to a standardised effect of size of approximately 0.4–0.42. Considering 90% power with the same power assumptions, we will be able to detect group differences in mean total PANSS score of between 6.9 and 7.3 (standardised effect size of 0.46–0.49).

As a secondary objective, we also wish to estimate the average treatment effect in those participants with a vitamin D deficiency at baseline. We assumed that 60% of the FEP population will have vitamin D concentrations below 50 nmol/L at baseline [23]. After 20% attrition at 6 months of the 60% who meet the vitamin D threshold, this will result in a projected sample size of 115. Based on alpha = 0.05, power = 80%, and samples with between 120 and 100 participants, we will confidently be able to detect differences in trial arms for mean total PANSS scores between 7.7 and 8.5 (effect size of 0.52–0.57). Considering 90% power with the same power assumptions, we will be able to detect group differences in mean total PANSS score between 8.95 and 9.8 (effect size of 0.60–0.65).

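### The listed primary model yields no 6-month PANSS contrast, and adding one under a random intercept with a single residual variance could miscalibrate its standard error

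*Protocol article*

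**What the plan says.** The Primary outcome section of the Protocol article is specific about the visit: "The primary outcome is symptom severity, as assessed via total PANSS scores at 6 months after randomisation". The Secondary outcomes section lists PANSS at 3 months as an outcome of its own, so the two visits are meant to be reported separately.

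The Statistical analysis section sets out the linear mixed model. On the data: "All the available follow-up data from the randomised participants will be modelled". On the fixed effects: "The analysis model will include treatment arm (vitamin D or placebo), time (3 or 6 months), baseline PANSS and randomisation stratifier (ethnicity) as explanatory variables". On the covariance: "The model will also contain a subject-varying random intercept to account for any correlation between the repeated measures". No product of arm and time is listed, and nothing is said about whether the residual variance is common to both visits. The same section leaves the rest to another document: "Full details of the statistical analyses will be specified in a statistical analysis plan written in collaboration with the trial statisticians".

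The Sample size section gives one SD for total PANSS, 15.0, from an external first-episode sample. It gives no SD by visit and no correlation with baseline.

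**The concern.** There are two linked issues.

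First, with arm and time as main effects only, the model has one arm coefficient, shared by 3 and 6 months. That coefficient does not estimate the declared primary quantity unless the treatment effect is the same at both visits.

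Second, adding the arm-by-time term repairs the first issue but brings the covariance into play. A random intercept with one residual variance is compound symmetry, which gives both visits the same variance. A contrast at 6 months is then judged against the average of the two variances. Because the model adjusts for baseline PANSS, the variances that must be equal are those conditional on baseline. Equal raw SDs are not enough if baseline predicts the 3-month score better than the 6-month score.

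At stake is the calibration of the primary test. Its interval would be too narrow if 6-month scores are the more variable, and too wide, with lost power, if they are the less variable.

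**Working it through.** **The plan's own figures.** With SD 15, two-sided alpha 0.05 and 80% power, the detectable difference is (1.960 + 0.842) × 15 × √(2/n).
- n = 100 per arm: 5.94 (5.97 by noncentral t).
- n = 90 per arm: 6.27 (6.30 by t).

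These match the stated 6 to 6.3. The sample size therefore rests on a comparison of two means with one SD, and nothing below changes it.

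**Inputs for the check.** From the article: 96 per arm after attrition. Assumed: residual SDs at 3 and 6 months given baseline, with variances v3 and v6, and a between-visit correlation of 0.6, so that the covariance is c = 0.6 × SD3 × SD6. The closed forms take complete data.

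**Listed model (one arm effect).** The estimate is the difference between arms in each participant's average over the two visits. Its true variance is (2/n)(v3 + v6 + 2c)/4. The compound-symmetry fit estimates the average variance and c, which gives the same expression. For SD 13/15, c = 117 and (169 + 225 + 234)/4 = 157, so the SE is √(2 × 157/96) = 1.809 both ways.

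**6-month contrast (arm-by-time added, one residual variance).** Model SE = √[(2/n)(v3 + v6)/2]. True SE = √[(2/n)v6]. Ratio R = √[((v3 + v6)/2)/v6]. Type I error = 2[1 − Φ(1.96R)].

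| SD at 3 / 6 months | Pooled effect: model and true SE | 6-month contrast: model SE | True SE | R | Type I error |
|---|---|---|---|---|---|
| 15 / 15 | 1.936 | 2.165 | 2.165 | 1.00 | 5.0% |
| 13 / 15 | 1.809 | 2.026 | 2.165 | 0.94 | 6.7% |
| 12 / 15 (ratio 1.25) | 1.746 | 1.961 | 2.165 | 0.91 | 7.6% |
| 15 / 12 (ratio 0.8) | 1.746 | 1.961 | 1.732 | 1.13 | 2.7% |
| 10 / 15 | 1.622 | 1.840 | 2.165 | 0.85 | 9.6% |

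At ratio 0.8, a test planned for 80% power has power Φ(2.802 − 1.96 × 1.132) = Φ(0.583) = 72%.

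**Equal raw SDs.** If the raw SD is 15 at both visits and the correlations with baseline are 0.7 and 0.5 (assumed), the residual variances are proportional to 1 − 0.49 = 0.51 and 1 − 0.25 = 0.75. Then R = √(0.63/0.75) = 0.917 and type I error is 7.2%. With correlations 0.5 and 0.4 the variances are 0.75 and 0.84, R = √(0.795/0.84) = 0.973, and type I error is 5.7%.

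**Simulation.**
- REML random-intercept fits, 120 per arm, 2,500 replicates per scenario, with complete data or about 10% and 20% missing at 3 and 6 months. The listed model had a ratio of mean SE to empirical SD of 0.97 to 1.02 and type I error of 4.6% to 5.8% in every scenario. The 6-month contrast had type I error of 6.6% (complete) and 7.0% (missing) at SD 13/15, 7.3% and 7.4% at 12/15, and 2.6% and 2.8% at 15/12.
- 3,000 replicates, 240 randomised, about 20% month-6 dropout depending on month-3 PANSS, SD 15 at both visits. With baseline correlations 0.7 and 0.5, type I error was 6.8% under compound symmetry and 4.7% under an unstructured covariance. With 0.5 and 0.4, compound symmetry gave 4.8%.
- A smaller run of the 0.7/0.5 case (600 replicates, Monte Carlo error about 1 percentage point) gave a mean SE of 1.66 against an empirical 1.85 under compound symmetry. The unstructured fit had 1.84 against 1.86.

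**The case against.** A reader might infer that the primary test fails to hold its 5% level whenever the two visit variances differ. The document does not support that. The model as listed has no 6-month contrast, and the effect it does contain keeps a correct SE with complete data and a nearly correct one under the missingness simulated. Every inflated figure above belongs to a model with an arm-by-time term that the article does not list.

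Nor does a random intercept strictly force equal variances. It can be fitted with visit-specific residual variances, and the article does not say which is meant.

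Unequal variances are also an assumption. The article gives one SD and nothing on how variance or correlation with baseline changes over time, and the direction of any error is unknown.

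Finally, covariance structure and degrees of freedom are commonly left to an analysis plan, and this article says that one will exist.

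All of this limits the claim, but two things remain. The article did not leave covariance wholly open: it named a device, ordinarily fitted with one residual variance, and an analysis plan that follows it inherits that. And the outcome sections call for separate 3- and 6-month effects, which the listed terms do not provide. Adding only the missing interaction would leave the 6-month SE exposed.

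**Conclusion.** The point holds as a mismatch and a conditional risk. The listed model estimates an arm effect averaged over 3 and 6 months with an essentially correct SE, while the declared primary outcome is the 6-month score. If the 6-month contrast is obtained by adding arm-by-time to a random-intercept model with one residual variance, its SE is miscalibrated to the extent that the conditional variances differ.

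Over the assumed range from SD 15/12 to 12/15, type I error runs from 2.7% to 7.6%; it is about 6.7% at 13/15, and the effect is negligible when the variances are close. These figures rest on SDs and correlations that the article does not give, so neither size nor direction can be stated for this trial. The stated sample-size figures reproduce and are unaffected. The change is worth making as a free improvement; no error in the primary test has been demonstrated.

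**What to change.** In the Statistical analysis section, and in the analysis plan that follows it:
- Add the arm-by-time term and define the primary effect as the arm contrast at 6 months. The 3-month contrast from the same model serves the secondary outcome.
- Replace the random intercept with an unstructured 2x2 residual covariance for the 3- and 6-month PANSS. A random intercept with visit-specific residual variances is equivalent when the covariance is non-negative and no larger than the smaller variance.
- Fit by REML with Kenward-Roger degrees of freedom.
- Use the same structure for the PANSS sub-scores.

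The cost is one extra covariance parameter (three instead of two), one fixed effect for arm-by-time, and a sentence or two of text, settled before unblinding. No further data or participants are needed, and the likelihood analysis still relies on data missing at random. The 6-month contrast has a larger SE than the pooled effect (2.165 against 1.936 at SD 15/15 and correlation 0.6), but planned power is not lost: 2.165 = 15 × √(2/96) is the SE implied by the sample-size method at 96 per arm.
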